## Abstract

The coronavirus disease 2019 (COVID-19) pandemic increased education-related distress among University students globally, including in Indonesia. Psychological factors, such as academic demands, limited opportunity to meet their peers, problematic use of technology, and domestic problems, influenced the well-being of the students, leading to poor academic performance. A mobile-based counseling application was developed to address the distress among University students. The application was meant to reach students living remotely to enable them to access psychological assistance. Therefore, the purpose of this study was to describe a protocol aimed to evaluate the equivalence of the application when compared to the Treatment-As-Usual (TAU) in increasing the coping self-efficacy (CSE) and resilience of students as well as in decreasing their level of depression. A two-armed parallel randomized control non-inferiority trial will be conducted among approximately 430 students with selected academic problems. The participants will be randomly allocated into the TAU and the intervention groups. The primary and secondary outcomes will be measured by the Indonesian versions of the Coping Self-Efficacy (CSE) Scale, the Resilience Scale (RS-14), and the Patient Health Questionnaire (PHQ-9). The data will be collected at baseline, at the end of each session, and after 3 months. The outcomes will be analyzed using repeated-measures ANOVAs, intention-to-treat, and per-protocol analysis. If proven, the application will be used as an alternative media in helping the students.

**Clinical Trial Registration:** Thailand Clinical Trials Registry (TCTR20200530001); Date of registration: May 28, 2020.

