According to several studies, online counseling is needed by students because they cannot access mental healthcare (Chan, 2020; Li and Leung, 2020; Novella et al., 2020). Although there are several limitations, the studies showed that online counseling is effective in dealing with psychological issues such as emotional distress, anxiety, and social withdrawal symptoms. The study aimed to test whether or not the mobile-based counseling application called “SAENA” can help the students increase their (1) CSE and (2) resiliency, as well as decrease their (3) level of depression. Therefore, the hypothesis is that the application is equivalent to the Treatment-As-Usual (TAU) in increasing the personal resources of students.

The quality of a study depends on how well-both the design and execution phases of the project are (Ott, 1991). By writing the protocol, a gap between these phases could be examined carefully and fairly. The protocol also helps the researchers in providing study documentation as well as in increasing the efficiency of the projects (Ott, 1991). Therefore, this study will explain the protocol of the non-inferiority trial of the mobile-based counseling application.

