## Materials and Methods

### Study Design

This study describes a study that will be conducted as a two-armed parallel randomized controlled non-inferiority trial. The trial is in line with the guidelines for the protocol content of the non-inferiority trial (Piaggio et al., 2012). It will also be based on the guidance of the Standard Protocol Items: Recommendations for Intervention Trials (SPIRIT) Statement (Tetzlaff et al., 2012; Chan et al., 2013). The non-inferiority scheme will be used in this study because the application is not aimed to be more powerful or effective than the usual treatment but aimed to increase the practicality of the counselors to store the data in the application and to hide personal contacts (e.g., email addresses or online meeting IDs) by solely using the application only for the counseling purposes (Hahn, 2012).

To eliminate the assay sensitivity, bias, and constancy assumption (ABC) of this non-inferiority trial, there are several things included in the design. First, the outcome measurement tools that will be used in both groups are reliable. Second, besides using randomizing in allocation and double-blinding procedure, the control group will get the TAU without any intervention to prevent a bias. Third, the data will be collected in the same period for both groups to minimize any situational effects, such as the COVID-19 pandemic-related government policies in this country (Walker, 2019).

The proposed study will be a parallel group design comparing two types of treatments. The intervention group will use the application whereas the control group will get the TAU. The intervention group will have three counseling sessions for a month; meanwhile, the control group will have many sessions based on the need of each individual. All outcomes will be assessed repeatedly using online self-reported forms, which will be facilitated by research assistants. The assessments will be taken (1) before the intervention, (2) after each session (a session/week), and (3) after 3 months. The study design is shown in Figure 1.

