### Data Analysis

Descriptive statistics will be used to describe relevant demographic data, such as the frequency and the percentage for the categorical data as well as the mean and the SD for the outcome measurements. There will be three analysis plans to prove the non-inferiority of the application, which are (1) repeated-measures ANOVAs (Goodman et al., 2016; Twisk et al., 2018), which will be used to test for differences between the TAU and the intervention groups (i.e., between-subjects factor) in the treatment at the four time points (i.e., within-subjects factor). We would like to assess whether the outcomes will be improved after treatment using the application and the TAU. An analysis will be conducted to check the constancy assumption. Then, both (2) the intention-to-treat (ITT) and (3) the per-protocol analysis will be performed. Previous studies showed that performing both analyses will produce more convincing results to conclude the non-inferiority of a new treatment (Hahn, 2012; Walker, 2019). The ITT analyses will be chosen to handle the missing value due to the protocol deviations, withdrawal, and non-compliance (Gupta, 2011) whereas the per-protocol analysis will minimize the factors that would make the two groups seem similar (Walker, 2019).

The statistical hypotheses in this non-inferiority trial use Δ. The null hypothesis states that the intervention using the application will be inferior to the TAU (H0: TAU–SAENA ≥ Δ). The alternative hypothesis states that the intervention will not be inferior (will have a similar effect) to the TAU although the effect may not be as good as the TAU within the extent of margin (H1: TAU–SAENA < Δ). Of note, 95% CI will be used. The interval will be the mean difference between the outcome measures of the two groups. The formula is as follows:

$$\begin{array}{l} \left(\mu_{saena}-\;\mu_{TAU}\right)\pm 1.96\sqrt{\frac{\sigma_{saena}^{2}}{n_{saena}}+\frac{\sigma_{TAU}^{2}}{n_{TAU}}} \end{array}$$

μ, mean; Tau, standard deviation; *n*, sample.

The 1.96 is the *z*-value, and the value from this formula can now be compared with Δ. If the interval remains above Δ, then the inferiority of the application will be proven according to the standards that have been set. In contrast, if the upper limit for treatment difference by the intervention group compared to the TAU group is < Δ, then the non-inferiority will be concluded.

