## Discussion

This study will provide the initial evidence of the equivalence of the mobile-based counseling application in improving the CSE and resilience as well as decreasing the level of depression among students with academic problems during the pandemic. While academic distress during the pandemic is the main focus of this study, the application is designed to be relevant to a broad range of mild psychological issues among young people.

The protocol modifications will be communicated after this study is performed. A trial registry amendment will be performed at the TCTR website. Since there was a limited study that tests the equivalency of a protocol in psychological intervention in Indonesia, this study would provide a standardized protocol for improving psychological aspects (i.e., the primary and secondary outcomes) among the students. Furthermore, this study would be very useful in helping people in this pandemic because it provides a protocol that requires no face-to-face condition to deliver counseling sessions.

There were several previous non-inferiority studies in the fields of online psychological intervention. The most common one is cognitive behavior therapy (CBT)-based interventions. Several studies show that the online CBT-based interventions are equivalent to the face-to-face CBT-based intervention with moderate to large effect size in helping participants to reduce insomnia and depression symptoms (Andersson et al., 2013; Wagner et al., 2014; Blom et al., 2015). Norwood et al. (2018) conducted a meta-analysis study regarding the non-inferiority trials on videoconferencing psychotherapy. The study shows that the videoconferencing psychotherapy is partly non-inferior while compared to the face-to-face psychotherapy. Moreover, a study was conducted by Mak et al. (2018) on the efficacy of a mobile application-based program on mental health. The application consisted of (1) mindfulness-based training; (2) self-compassion training; and (3) cognitive-behavioral psychoeducation. This study shows that the application-based program is efficacious in improving well-being. However, this study does not take the non-inferiority margin as a criterion to analyze the non-inferiority of treatment. As a result, this proposed study will enrich the non-inferiority evidence of the online-based SFBT.

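### Aim, hypothesis and Discussion speak of equivalence to TAU, but the formal test is one-sided non-inferiority; the wording should match the test

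*Protocol article*

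**What the plan says.** Three statements about what this trial is for use the language of equivalence:

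- Abstract, purpose: to "evaluate the equivalence of the application when compared to the Treatment-As-Usual (TAU") in raising coping self-efficacy and resilience and lowering depression.
- Introduction, hypothesis: "the hypothesis is that the application is equivalent to the Treatment-As-Usual (TAU) in increasing the personal resources of students".
- Discussion, opening: "This study will provide the initial evidence of the equivalence of the mobile-based counseling application". The same section later places the trial among the few Indonesian studies of equivalency in psychological intervention.

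The operative parts say something else. Under Study Design the trial will be "conducted as a two-armed parallel randomized controlled non-inferiority trial". Under Data Analysis, "The null hypothesis states that the intervention using the application will be inferior to the TAU (H0: TAU–SAENA ≥ Δ"). The alternative reads "The alternative hypothesis states that the intervention will not be inferior (will have a similar effect) to the TAU", and the sentence goes on: "although the effect may not be as good as the TAU within the extent of margin (H1: TAU–SAENA < Δ"). Non-inferiority is concluded when the upper confidence limit for the treatment difference is below Δ, using a 95% CI. Repeated-measures ANOVAs are also listed, to test for differences between the arms.

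**The concern.** Equivalence and non-inferiority are different claims. Equivalence says that the difference is small in both directions. Non-inferiority says only that the new treatment is not worse by Δ or more. A reader of the Abstract or Discussion would expect evidence for the first, while the Data Analysis section can deliver only the second.

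What is at stake is the claim made from a positive result. If the report takes its wording from the aim and hypothesis, it will assert equivalence, which no planned test examines. The parenthesis about a similar effect in the alternative hypothesis invites the same slip, because that hypothesis is also true when the application is much better than TAU.

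**Working it through.** **1. The statements side by side**

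| Place in the protocol | What is to be shown | Bounds on the difference |
|---|---|---|
| Abstract, purpose | Equivalence | None stated |
| Introduction, hypothesis | Equivalence | None stated |
| Discussion, opening | Equivalence | None stated |
| Study Design | Non-inferiority | – |
| Data Analysis, H0 and H1 | Non-inferiority | One: TAU − SAENA < Δ |
| Data Analysis, decision rule | Non-inferiority | One limit against one margin |

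No second margin, pair of one-sided tests, or requirement that the whole interval lie within ±Δ appears anywhere. The interval formula is written SAENA − TAU while the hypotheses are written TAU − SAENA. That is a separate matter: in either orientation, the non-inferiority conclusion uses one limit only.

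**2. What the sample size was built for**

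Inputs from Participants: SD 1, Δ = 0.24, 215 per arm. Two assumptions are needed: the 80% figure given there is read as power, and the one-sided alpha, which is not stated, is taken as 0.05 because that value reproduces the result.

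n per arm = 2 × SD² × (z₀.₉₅ + z₀.₈₀)² / Δ² = 2 × (1.6449 + 0.8416)² / 0.24² = 2 × 6.183 / 0.0576 = 214.7, rounded up to 215.

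This matches the protocol's figure, and it is a non-inferiority calculation.

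**3. Passing the planned test does not imply equivalence**

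SE = √(2/215) = 0.0964. Suppose the application were truly 0.24 SD better than TAU, with Δ = 0.24 and a 95% CI:

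- P(non-inferiority shown) = Φ((0.24 + 0.24)/0.0964 − 1.96) = 99.9%.
- For the whole interval to lie within ±0.24, the estimate must lie within ±(0.24 − 1.96 × 0.0964) = ±0.051. With a true difference of 0.24, that probability is 2.4%.

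So the planned test can succeed almost every time when the arms are not similar in the two-sided sense.

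**4. Illustration with no true difference**

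The symmetric margin here is my assumption. Both values of Δ are shown because Participants gives 0.24 and the margin section gives 0.22, which is a separate inconsistency.

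P(95% CI wholly within ±Δ) = 2Φ(Δ/SE − 1.96) − 1

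- Δ = 0.22: 2Φ(2.281 − 1.96) − 1 = 2 × 0.626 − 1 = 25%.
- Δ = 0.24: 2Φ(2.489 − 1.96) − 1 = 2 × 0.701 − 1 = 40%.

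**The case against.** The strongest reply is that the authors simply use the two words interchangeably. The Abstract calls the study a non-inferiority trial directly after stating the equivalence aim, the Introduction closes by calling it one, and the Discussion says it will add to non-inferiority evidence. The decision rule itself concludes non-inferiority. The practical goal, offering the application as an alternative medium, needs no more than that. The parenthesis about a similar effect is qualified in the same sentence, which allows the application to be somewhat worse within the margin. The protocol proposes no ±Δ region, so power for equivalence measures something it never set out to do.

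Most of this stands, and it rules out stronger readings that a reader might infer:

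- **That the trial cannot support its conclusion.** The conclusion written into Data Analysis is non-inferiority, and the test is of the right form for it.
- **That the plan directs a positive result to be reported as equivalence.** No such rule exists, and the stated rule reports non-inferiority.
- **That one-sided non-inferiority is the only test.** ANOVAs are planned too, although a test of difference cannot establish equivalence.
- **That the trial is undersized for its purpose because equivalence power is low.** That power depends on a margin the protocol does not set.

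The mismatch itself remains. Interchangeable use in the aim, the hypothesis and the promised evidence is the fault, because those statements fix what the trial will be said to have shown. The qualification in the alternative hypothesis covers only the side on which the application is worse; it sets no limit on how much better it may be, so *similar* is still wrong.

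**Conclusion.** The concern holds as an inconsistency between the stated claim and the planned test. Three statements (purpose, hypothesis, promised evidence) say equivalence, while the design label, hypotheses and decision rule say one-sided non-inferiority. The non-inferiority conclusion is supportable in form; the equivalence conclusion is not, because the difference is bounded on one side only. This goes beyond a clerical slip, since it changes what the trial may claim, but it exposes no flaw in the choice of a non-inferiority design.

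The conclusion rests on the text alone. The 25% to 40% range is illustrative and depends on the assumed symmetric margin, SD 1, 215 per arm and a true difference of zero.

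**What to change.** - In the Abstract (purpose), the Introduction (hypothesis) and the Discussion (opening sentence and the later mention of equivalency), replace equivalence, equivalent and equivalency with non-inferiority or non-inferior where they describe this trial. Descriptions of other studies' findings can stay.
- In Data Analysis, delete the parenthesis about a similar effect from the alternative hypothesis and keep the rest of the sentence.

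Once the wording is corrected, no separate rule for claiming equivalence is needed. The change requires no additional participants, assessments or analyses. Its cost is a slightly weaker claim: not worse than TAU by the margin or more, rather than equivalent to it.

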## Introduction

The coronavirus disease 2019 (COVID-19) pandemic influenced many aspects of human health as follows: infecting many people, causing severe disease, and increasing mortality rate, especially among vulnerable people (World Health Organization, 2020). Also, the pandemic disrupts other aspects of human life, since the virus is transmitted between people through indirect, direct, and close contact. Therefore, the human movement was limited, such as social and economic activities. People stayed at home to avoid contact with other people, though this social isolation may lead to adverse psychological conditions. According to Tull et al. (2020), people tend to be anxious, worried, and lonely under stay-at-home order. Another study showed that during this situation, there are significant changes in the sleep and work patterns of people. The total sleep time and screen time decrease and increase, respectively, thereby affecting their moods significantly (Conroy et al., 2021). Park et al. (2020) stated that the pandemic increases the uncertainty that affects well-being and stress.

Furthermore, several studies conducted during the pandemic showed that the prevalence of mental health issues among University students has increased (Chen et al., 2020; Son et al., 2020). The majority of respondents perceive stress, anxiety, and depression. There are several sources of stress (Misra and Castillo, 2004; Stevenson and Harper, 2006), such as (1) worrying about health conditions; (2) feeling isolated; and (3) concern about the academic workloads and performances. The academic-and non-academic-related stress causes several problems among the students though not limited to lowered grades and dropped courses (The American College Health Association, 2009). Also, it reduces well-being (Misra and Castillo, 2004; Stevenson and Harper, 2006).

Personal resources, such as self-mastery or coping self-efficacy (CSE), are important in lowering distress and apprehension during the pandemic (Ben-Ari and Ben-Yaakov, 2020). Generally, CSE refers to the confidence in one's own ability to carry out various coping strategies and execute a course of action designed to manage an external stressor (Watson and Watson, 2016). This personal resource aligns with the self-efficacy concept (Bandura, 2002), which leads to having better effort, persistence, and resistance. Moreover, the CSE enables students to exhibit positive strategies to manage adversities in their lives, including during the pandemic (Watson and Watson, 2016). A study showed that students with better CSE have better adjustment and less stress (Denovan and Macaskill, 2013).

Generally, the studies of students suggested the need for the support of universities to help manage stress during the long-lasting pandemic being studied (Pajarianto et al., 2020; Son et al., 2020). The interventions need to fit the stay-at-home situation and the characteristics of young people. Consequently, the University students are categorized as Generation Z, who were born between 1995 and 2000 (Hampton and Keys, 2017). They become familiar with the digital world at a young age and, hence, are the most electronically connected generation (Geck, 2006). The students are already getting used to communicating, collaborating, or interacting through the Internet (Hampton and Keys, 2017). Also, these characteristics are true for Generation Z in Indonesia (Hinduan et al., 2020). Among the electronic devices, the smartphone is the most frequent device used every day, and it accounted for 3.5 h/day before the pandemic (Zaenudin, 2017). The Internet, especially smartphones, is a promising media to focus on in designing the new intervention effective for University students during the pandemic.

According to several studies, online counseling is needed by students because they cannot access mental healthcare (Chan, 2020; Li and Leung, 2020; Novella et al., 2020). Although there are several limitations, the studies showed that online counseling is effective in dealing with psychological issues such as emotional distress, anxiety, and social withdrawal symptoms. The study aimed to test whether or not the mobile-based counseling application called “SAENA” can help the students increase their (1) CSE and (2) resiliency, as well as decrease their (3) level of depression. Therefore, the hypothesis is that the application is equivalent to the Treatment-As-Usual (TAU) in increasing the personal resources of students.

The quality of a study depends on how well-both the design and execution phases of the project are (Ott, 1991). By writing the protocol, a gap between these phases could be examined carefully and fairly. The protocol also helps the researchers in providing study documentation as well as in increasing the efficiency of the projects (Ott, 1991). Therefore, this study will explain the protocol of the non-inferiority trial of the mobile-based counseling application.

## Materials and Methods

### Study Design

This study describes a study that will be conducted as a two-armed parallel randomized controlled non-inferiority trial. The trial is in line with the guidelines for the protocol content of the non-inferiority trial (Piaggio et al., 2012). It will also be based on the guidance of the Standard Protocol Items: Recommendations for Intervention Trials (SPIRIT) Statement (Tetzlaff et al., 2012; Chan et al., 2013). The non-inferiority scheme will be used in this study because the application is not aimed to be more powerful or effective than the usual treatment but aimed to increase the practicality of the counselors to store the data in the application and to hide personal contacts (e.g., email addresses or online meeting IDs) by solely using the application only for the counseling purposes (Hahn, 2012).

To eliminate the assay sensitivity, bias, and constancy assumption (ABC) of this non-inferiority trial, there are several things included in the design. First, the outcome measurement tools that will be used in both groups are reliable. Second, besides using randomizing in allocation and double-blinding procedure, the control group will get the TAU without any intervention to prevent a bias. Third, the data will be collected in the same period for both groups to minimize any situational effects, such as the COVID-19 pandemic-related government policies in this country (Walker, 2019).

The proposed study will be a parallel group design comparing two types of treatments. The intervention group will use the application whereas the control group will get the TAU. The intervention group will have three counseling sessions for a month; meanwhile, the control group will have many sessions based on the need of each individual. All outcomes will be assessed repeatedly using online self-reported forms, which will be facilitated by research assistants. The assessments will be taken (1) before the intervention, (2) after each session (a session/week), and (3) after 3 months. The study design is shown in Figure 1.

